### Primary outcome

The primary outcome measure is the number of healthcare contacts taking place in the four-week period following the index same-day consultation request. The number of contacts will include the initial clinical assessment contact, and will thus include the triage contact in the two intervention conditions. The total number of contacts per 1,000 patients requesting same-day consultations in each of the trial conditions will be derived from numbers of GP, practice nurse, GP out-of-hours, A&E, and (although they may not impact significantly on GP workload
[36]) NHS WIC attendances. Data collection, capturing information on timing (am/pm), and type (face-to-face, telephone, home visit, GP out-of-hours, A&E and WIC attendance) of primary care contacts in all trial practices will take place as part of a note review occurring at least twelve weeks after the index consultation request with data extracted from the primary care medical record. We will count the day of the index request as day 1 (same day), and include the following 28-day period (day 1 to day 28 inclusive) starting from the day following the consultation request.

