### Data collection

#### Clinician data collection forms

Clinicians will complete a short data collection form (clinician form) at the time of the initial consultation following a patient’s same-day request (triage or usual care contact). This form captures details of the consultation including which health professional undertook the consultation, whether the patient did not attend, case-mix (see Secondary outcomes, Descriptive data), treatment and management options chosen (for example, ordering of tests, recommending subsequent appointment or referral), start and end time of the consultation and the patient’s response to the initial verbal consent to note review, which the clinician asks for at the end of the consultation.

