The influence of practice-level characteristics (for example, deprivation, location and list size) on the primary outcome will be investigated using interaction terms. Although the power to detect moderate subgroup interactions will be low, we are primarily interested in investigating the possibility of large interactions, which are qualitative (the direction of treatment effects varies between subgroups) rather than quantitative (the magnitude of the treatment effect varies between subgroups, but not the direction). This subgroup analysis will be restricted to the primary outcome.

Sensitivity analyses will be conducted to investigate the potential impact of missing data on the primary outcome only. These will include making different assumptions such as best-case scenarios (for example, assuming a patient who does not consent to a case notes review has zero healthcare contacts in the four-week period following the initial telephone call requesting a same-day appointment), as well as multiple imputation models. Available demographic characteristics (depending on whether questionnaire is completed) of patients who consent to the case notes review will be compared to those who do not.

The primary economic analysis will estimate the mean cost of care across each of the trial arms, to include triage (where used) and the items in the primary outcome. Economic analyses will be based on a micro-level costing estimate for the triage intervention, and the use of published unit cost data for other elements of resource use. Estimates of the cost associated with triage interventions will be based on incremental costs when compared to usual care, with any capital costs and/or training costs depreciated/spread over an appropriate time period in the primary analyses (with other time horizons for these costs explored in sensitivity analyses).

The economic evaluation will present between group comparisons of costs using the regression-based statistical methods described above. Mean participant-level cost estimates for the triage interventions will be presented, with 95% CI. Although cost data often does not follow a normal distribution and parametric tests are therefore not appropriate, if a sample has a large number of observations as in this case (circa 18,000), incorporating central limit theorem implies parametric tests are appropriate and may be used
[9].

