### Informed consent

Practice recruitment arrangements are described previously. All patients requesting same-day consultations over the five-week recruitment period in the study practices will be eligible for inclusion in the study (subject to the age limits specified above).

When patients call the practice seeking a same-day consultation the receptionist will advise them (or the guardian of children aged less than 12 years) of the current practice consultation arrangements. Once it has been ascertained that the patient does not require urgent or emergency care, the receptionist will explain briefly that a trial is taking place and advise the patient that the practice would appreciate them participating in a questionnaire survey, which will be sent to them for their consideration within around four weeks. The consulting (triage/usual care) clinician will reiterate that patients may be sent a questionnaire to ask their opinion of the triage system/existing consulting arrangements, and will ask patients at the end of the clinical interaction whether they would be agreeable to a researcher reviewing their notes in twelve weeks time. The patient’s verbal consent will be noted on a data collection form. Four weeks later the practice will send patients an information sheet describing the study, a questionnaire and a prepaid return envelope. Participants may opt out of the notes review on the last page of the questionnaire, should they wish to do so at that stage. A name with contact details will be provided should patients require any further information and those who do not wish to complete a questionnaire will be encouraged to return their blank questionnaire in the prepaid envelope, and they will receive no further contact in relation to the study. Those who do not respond to the questionnaire will be sent a second and third mail-out of the questionnaire and information sheet two and four weeks later.

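### The best-case example for missing outcomes gives zero contacts to patients who have normally had at least one, and it does not bound the treatment difference

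*Protocol article*

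**What the plan says.** The Statistical analysis section of the protocol article plans sensitivity analyses for missing data on the primary outcome only. They consist of "making different assumptions such as best-case scenarios", "as well as multiple imputation models", and a comparison of patients who do and do not consent to note review. The one scenario spelled out is "assuming a patient who does not consent to a case notes review has zero healthcare contacts in the four-week period", counted from the telephone call that requests the appointment. No distinction by arm is made.

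Three other places bear on it:

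- Primary outcome: "The number of contacts will include the initial clinical assessment contact, and will thus include the triage contact in the two intervention conditions".
- Informed consent (and Patient recruitment, to the same effect): the clinician "will ask patients at the end of the clinical interaction whether they would be agreeable to a researcher reviewing their notes". A second route out comes four weeks later: "Participants may opt out of the notes review on the last page of the questionnaire".
- Clinician data collection forms: the form for the first consultation records the reply on consent and also "whether the patient did not attend".

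**The concern.** A sensitivity analysis for missing data should give the missing patients values that they could have had, and should show how far the comparison could move. The stated example does neither. It gives most non-consenters a value that the outcome definition excludes. It also gives the same value in every arm, so what it changes depends on how many patients consented in each arm and not on how non-consenters might differ between arms.

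About 22% of patients are expected not to agree to note review (Sample size section: 78% under the revised consent arrangements). A result labelled best-case for that share of the data could be read as evidence of robustness or fragility when it mainly reflects consent shares. A gap in consent between arms is conceivable: practitioners are not blinded (Blinding section), and the request follows a triage contact in two arms and a usual-care contact in the third.

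**Working it through.** **Is zero possible?** Consent is sought at the end of the first clinical contact. That contact falls inside the follow-up window, which opens with the telephone request, and it counts toward the outcome. Refusal at that moment therefore implies a count of at least 1. A patient who opts out in the questionnaire four weeks later has normally been assessed too. A true zero needs a patient who did not attend or was never reached.

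**Inputs.** Sample size section: usual care m0 = 1.02 (SD 0.78); nurse triage m1 = 1.38 (SD 1.79); expected consent 78%. Consent by arm is not given; the unequal pairs below are assumptions.

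**Check on the inputs.** n per group = (0.78² + 1.79²)(1.96 + 1.28)² / 0.36² ≈ 309, or 310 when rounded up by the sample-size routine, against the stated 305 (within 2%). 305 × 12.3 = 3,751.5, against 3,751. The means and SDs are therefore read as the plan uses them.

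**Formula.** Let c0 and c1 be the consent shares in usual care and triage, and let v be the single value given to non-consenters in both arms:

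difference = c1(m1 − v) − c0(m0 − v)

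With c0 = c1 = c this is c(m1 − m0), whatever v is.

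| Consent, usual care / triage | v = 0 | v = 1 |
|---|---|---|
| 78% / 78% | 0.78 × 0.36 = 0.281 | 0.78 × 0.36 = 0.281 |
| 83% / 73% (assumed) | 0.73 × 1.38 − 0.83 × 1.02 = 0.161 | 0.73 × 0.38 − 0.83 × 0.02 = 0.261 |
| 73% / 83% (assumed) | 0.83 × 1.38 − 0.73 × 1.02 = 0.401 | 0.83 × 0.38 − 0.73 × 0.02 = 0.301 |

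- With v = 0 and 78% consent, the usual-care mean is 0.78 × 1.02 = 0.796, below the minimum of 1 for anyone assessed.
- With no true effect and a common mean of 1.02, an 83% / 73% split with v = 0 gives (0.73 − 0.83) × 1.02 = −0.10.
- GP triage, planned as a 30% reduction (0.714 against 1.02, difference −0.306), becomes 0.78 × (−0.306) = −0.239 at equal consent.

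**Ratio scale.** With v = 0 the rate ratio is (c1/c0)(m1/m0). At equal consent it stays at 1.38/1.02 = 1.353, so the scenario tests nothing. At 83% / 73% it is 1.19.

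**Does it bound the effect?** Suppose 78% consent in both arms, and non-consenters averaging one contact more than consenters in one arm only. If that arm is usual care, the difference is 0.36 − 0.22 × 1 = 0.14. If it is triage, it is 0.36 + 0.22 × 1 = 0.58. The equal-consent zero scenario shows 0.281, which is neither limit.

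**Dependence on the planning means.** If the cited means leave out the index contact and both rise by 1 (2.02 and 2.38), equal consent still gives 0.281. The 10-point gaps give 0.061 or 0.501 with v = 0, and 0.161 or 0.401 with v = 1.

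**The case against.** - *It is an example in a summary.* The scenario is one of several assumptions, multiple imputation stands beside it, and the article says that a full analysis plan exists. This stands. The full plan may contain arm-specific or worst-case scenarios, so their absence from the article is no finding. It does not make the stated example valid.
- *The shrinkage is not caused by the zero.* This stands. At equal consent, 0.36 becomes 0.281 for any common value, including 1. Only the unequal-consent results depend on the value chosen.
- *The scale is open.* The article leaves family and link to be chosen. Shrinkage applies to a difference in means; with zero and equal consent a log-link ratio does not move.
- *Zero is not always impossible.* This stands for non-attenders and patients never reached. Where no clinician form was completed, a minimum of 1 is not documented either.
- *The planning means fit a floor of 1 poorly.* A mean of 1.02 with SD 0.78 leaves almost no room above 1, and the assumed GP-triage mean of 0.714 lies below it. The figures come from an earlier trial used as a proxy. The sizes shown are therefore illustrative; the conflict between the definition and the zero does not rest on them.
- *Best case may simply mean lowest workload.* Even so, the lowest count for an attended patient is 1, and a common low value still says little about the comparison between arms.

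**Conclusion.** The point holds in a limited form. The stated example contradicts the outcome definition for attended patients who decline note review. Used alike in all arms, it is a best case for no comparison and not a bound. At the expected 78% consent, equal by arm, it takes a mean difference of 0.36 to 0.28. Under an assumed 10-point gap it gives 0.16 or 0.40, where a floor of 1 gives 0.26 or 0.30. How much a floor helps depends on the means lying near 1; with both means one contact higher, it narrows the range from 0.06–0.50 to 0.16–0.40.

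A reader might infer three stronger things that the documents do not support:

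- That the whole missing-data strategy fails or the primary analysis is biased. Neither rests on this scenario.
- That up to 37% of outcomes will be missing. That is the complement of the 63% consent estimate, which the revised arrangements supersede; 22% is the current expectation.
- That consent will in fact differ by arm. No arm-level rates are given.

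**What to change.** In the Statistical analysis section, replace the zero-contact example as follows:

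1. Where the clinician form records an attended first contact, use a minimum of 1 contact for a non-consenter.
2. Keep 0 only where the form records non-attendance and no other contact is known.
3. Where no form was completed, assume neither value and impute.
4. Make the extreme scenarios arm-specific. One way is to shift the already planned multiple imputations separately by arm over a range stated in advance, and to report the shift at which the conclusion changes. The documents give no basis for a particular range, so the trial team must choose and justify it.
5. Report consent shares by arm beside these results, and state whether each result is a difference or a ratio.

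The cost is a little extra analysis. Attendance and the reply on consent are already on the clinician form where one was completed, so no new data collection is needed, and the primary analysis and planned multiple imputation stay as they are.

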**Methods/design:**

ESTEEM is a pragmatic, multi-centre cluster randomised clinical trial with patients randomised at practice level to usual care, computer decision-supported nurse triage, or GP-led triage. Following triage of 350–550 patients per practice we anticipate estimating and comparing total primary care workload (volume and time), the economic cost to the NHS, and patient experience of care, safety, and health status in the 4-week period following the index same-day consultation request across the three trial conditions.

We will recruit all patients seeking a non-emergency same-day appointment in primary care. Patients aged 12.0–15.9 years and temporary residents will be excluded from the study.

The primary outcome is the number of healthcare contacts taking place in the 4-week period following (and including) the index same-day consultation request. A range of secondary outcomes will be examined including patient flow, primary care NHS resource use, patients’ experience of care, safety, and health status.

The estimated sample size required is 3,751 patients (11,253 total) in each of the three trial conditions, to detect a mean difference of 0.36 consultations per patient in the four week follow-up period between either intervention group and usual care 90% power, 5% alpha, and an estimated intracluster correlation coefficient ICC of 0.05. The primary analysis will be based on the intention-to-treat principle and take the form of a random effects regression analysis taking account of the hierarchical nature of the study design. Statistical models will allow for adjustment for practice level minimisation variables and patient-level baseline covariates shown to differ at baseline.

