## Methods/design

### Design

The study is a pragmatic, three-arm, cluster RCT. Practices will be randomised 1:1:1 to receive GP-led triage, nurse-led computer based triage, or usual practice.

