### Sample size

Our estimation of sample size is based on the primary outcome of the number of healthcare contacts taking place in the four-week period following the index same-day consultation request. The estimation draws on a previous UK study comparing nurse-led telephone triage to standard practice for handling same-day consultation requests
[3]. That trial reported the number of NHS consultations based on general practice (GP and nurse), A&E and out-of-hours contacts. We believe this to be a good proxy for our primary outcome. Over the four-week follow-up of the trial the authors reported a mean number of NHS consultations of 1.02 (pooled SD 0.78) (Table four in
[3]) in usual care compared to a mean of 1.38 (pooled SD 1.79) in the nurse telephone-triage arm. Estimated trial sample size requirements for this trial are summarised in the table below. Four sample size scenarios are shown based on 80% or 90% statistical power and a intracluster correlation coefficient (ICC) of 0.01 or 0.05 (chosen as they represent the upper end of the average ICC reported from a survey across a range of outcome measures collected in trials from primary care settings
[46]) (see Table
1).

**Table 1 T1:** Sample size calculation

**Number per group***	**ICC**	**Design factor**	**Number of patients per group**	**Final number of patients per group+**	**Number of practices per group**
305*	0.01	3.26	994	1,867	4
305*	0.05	12.3	3,751	7,046	14
228^	0.01	3.26	743	1,396	3
228^	0.05	12.3	2,804	5,267	10

*At 90% power and 5% alpha; ^80% power and 5% alpha (both using the above means and SDs as per text); +after 6%
[3,27,28] of patients being excluded, 10%
[14,28,29] initially declining participation, 30%
[27-29] non-response to the request to return written consent to note review; of responders, 10% decline note review.

Selecting the most conservative sample size scenario (that is, 90% power, ICC 0.05) we estimate we require 3,751 patients per group to detect a difference of the magnitude reflected above (1.02 (0.78) versus 1.38 (1.79) primary care contacts in the follow-up period) in the primary outcome between the nurse-led triage and usual care arms. In order to inform the power study, and prior to undertaking the one-year pilot study (including the requirement for patient-written, rather than verbal consent), which would yield supporting data, we estimated that of all patients requesting a same-day consultation, 6%
[3,27,28] will be deemed ineligible, 10%

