Sensitivity analyses will be undertaken to explore the implications of uncertainty in data used, and assumptions made within the analyses. Exploratory analyses will be undertaken to estimate the costs associated with same-day primary care resource use, using trial data from the primary analyses combined with unit cost data, and also using data collected within the trial on a sample of same-day GP and nurse contacts (triage arms and usual care) to inform a more micro-level estimate of time spent in primary care on the same day as the triage index consultation.

Emphasis will be placed on estimation rather than hypothesis testing. Where hypothesis tests are carried out, these will be at the 5% level for primary and secondary outcomes, and the 1% level for interaction terms. While we adjust *P*-value cutoffs for the three-arm nature of this trial (that is, three independent between-group comparisons) we will not adjust for multiplicity of outcomes as such methods are too conservative when outcomes are positively correlated, as they would be in this trial. However, all analyses will be planned a priori and reported in full. All analyses will be conducted using Stata v.11. No interim analyses are planned.

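### The 90% power is calculated at an unadjusted 5% alpha, but the plan will adjust its P-value cutoffs for three comparisons; at such a cutoff the power is about 80%

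*Protocol article*

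**What the plan says.** **Sizing.** The Sample size section takes its effect from an earlier nurse-triage trial: "1.02 (0.78) versus 1.38 (1.79) primary care contacts in the follow-up period". Table 1 gives 305 per group before clustering and 3,751 after a design factor of 12.3, and its footnote sets the error rates: "At 90% power and 5% alpha; ^80% power and 5% alpha (both using the above means and SDs as per text". The text then adopts this row: "Selecting the most conservative sample size scenario (that is, 90% power, ICC 0.05) we estimate we require 3,751 patients per group". No allowance for more than one comparison appears in the section or the table. The Abstract extends the claim to both active arms, describing a 0.36 difference "between either intervention group and usual care 90% power, 5% alpha, and an estimated intracluster correlation coefficient ICC of 0.05".

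**Design.** "Practices will be randomised 1:1:1 to receive GP-led triage, nurse-led computer based triage, or usual practice". The Aims list three objectives: nurse triage against usual care, GP triage against usual care, and nurse against GP triage. These are all the pairwise contrasts of three arms.

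**Testing.** Of hypothesis tests, the Statistical analysis section says "these will be at the 5% level for primary and secondary outcomes". It then says the trial will adjust P-value "cutoffs for the three-arm nature of this trial (that is, three independent between-group comparisons) we will not adjust for multiplicity of outcomes". The article does not name the adjustment method.

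**The concern.** Power belongs to a particular test at a particular cutoff. If the primary contrasts are judged at a cutoff stricter than 5%, a sample size worked out at 5% does not deliver the power claimed for it. The 90% would then describe a test that the trial does not intend to run, and readers would be misled about how likely the trial was to detect a 0.36 difference, above all if the result is null.

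A smaller point sits in the same sentence. It calls the three comparisons independent. Each pair of contrasts shares an arm, and the third contrast is the difference of the other two, so they are correlated by construction. A cutoff derived from independence is stricter than it needs to be.

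**Working it through.** **Inputs.** Means 1.02 and 1.38, so the difference is 0.36; SDs 0.78 and 1.79; 90% power; 5% alpha; 305 per group before clustering; design factor 12.3 at ICC 0.05 (Sample size section and Table 1). Three comparisons (Statistical analysis). The calculations use the normal approximation.

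**1. Reproduce the plan's figure.**
- Sum of variances: 0.78² + 1.79² = 0.6084 + 3.2041 = 3.8125.
- n per group = 3.8125 × (1.960 + 1.282)² / 0.36² = 309, against the stated 305 (within 3%).
- At 80% power the same formula gives 231, against the stated 228.
- One-sided 5% at 90% power gives 252, which does not match.
- 305 × 12.3 = 3,751.

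The stated size is therefore that of an unadjusted two-sided 5% test.

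**2. Power at the plan's own effective size.** Standardised difference = 0.36 / √(3.8125/305) = 3.22. Power = Φ(3.22 − critical value).

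| Cutoff | Per-comparison alpha | Critical value | Power |
|---|---|---|---|
| Unadjusted | 0.05 | 1.960 | 89.6% |
| Bonferroni, three tests | 0.0167 | 2.394 | 79.6% |
| Sidak, three tests | 0.0170 | 2.388 | 79.7% |
| Tukey-type, correlation allowed for | about 0.019 | 2.344 | about 81% |

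**3. Size that would keep 90% at 0.0167.** n = 3.8125 × (2.394 + 1.282)² / 0.36², which rounds up to 398. Then 398 × 12.3 = about 4,895 analysed per group, against 3,751. The plan's attrition leaves 0.94 × 0.90 × 0.70 × 0.90 = 0.533, so 4,895 / 0.533 = about 9,185 per group, against 7,046. At 7,046 / 14 = 503 patients per practice, that is 18 to 19 practices per group, against 14.

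**4. Cost of the word independent.** With equal variances the contrasts have correlations of ±0.5. Bonferroni at 0.0167 then gives a familywise error of about 4.4% rather than 5%. Allowing for the correlation moves the cutoff to about 0.019 and raises power by just over 1 point (79.6% to about 81%).

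**5. Where the shortfall does not apply.**
- *GP arm under the 30% assumption.* The plan needs 1,983 for 90% power at 5% and recruits for 3,751 per group. Taking 1,983 as per arm (the less favourable reading), the standardised difference is 3.242 × √(3,751/1,983) = 4.46, and power at 0.0167 is Φ(4.46 − 2.394) = 98%.
- *Pilot ICC of 0.03.* A design factor of 12.3 at ICC 0.05 implies 1 + 11.3/0.05 = 227 patients per practice. At ICC 0.03 the factor is 1 + 226 × 0.03 = 7.78, and power at 0.0167 is 95%. With 3,751/14 = 268 per practice it is 91%. With a t reference on 26 df these become 92% and 88%.

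**The case against.** The strongest reply has four parts.

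*The adjustment method is unnamed because the article only summarises a fuller plan.* This is fair, and the missing name is not itself the fault. But any fixed cutoff for three comparisons lands at 80 to 81%, so the finding does not depend on which one is meant. A gatekept or closed procedure could keep 5% per pair, but that is not the natural reading of adjusting cutoffs.

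*The design is already conservative.* The plan chose ICC 0.05 as its cautious scenario; the pilot gave 0.03, and revised consent arrangements raise the expected note-review rate from 63% to 78%. This limits the practical harm. However, the pilot interval (0.00 to 0.08) includes 0.05, and the 90% is claimed at 0.05.

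*The section puts estimation ahead of testing.* That lowers the stakes, but the trial is still sized on the power of a test.

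*Independent may loosely mean separate.* Possibly. The numerical effect is small either way, and the power gap comes from alpha, not from this word.

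A reader might also infer three stronger things that the document does not support:
- **That the two sentences on test levels contradict each other.** They do not: a 5% familywise level with adjusted cutoffs for individual comparisons fits both.
- **That familywise error is about 12%.** That is the figure for unadjusted pairwise tests at 5%, and the plan says it will adjust.
- **That power falls to between 63% and 72%.** Those values also include a separate discrepancy in the design factor (227 against 268 patients per practice) and, at the lower end, small-cluster corrections. In a simulation with 14 practices of 268 per arm, unadjusted power is already only about 80%.

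**Conclusion.** The concern holds for the stated power. The 305 and 3,751 give 90% for a 0.36 difference only at an unadjusted two-sided 5% alpha. With the adjustment the plan announces, the same numbers give about 80 to 81%, a loss of 9 to 10 points. This assumes a fixed cutoff for three comparisons, the plan's SDs, its design factor of 12.3 at ICC 0.05, and a normal approximation.

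The scope is nurse triage against usual care, which sets the size, and either active arm against usual care in so far as the Abstract makes the 0.36 claim for both. It does not extend to the GP arm under its separate 30% assumption. No power is claimed for nurse against GP triage. Type I error is not at risk, because the announced adjustment protects it. Calling the contrasts independent is incorrect, but costs only about 1 point of power.

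**What to change.** In the Statistical analysis section, state that 5% is the familywise level for the three pairwise contrasts of the primary outcome, name the procedure, give the per-comparison alpha, and delete the word independent. In the Sample size section and Abstract, restate the power at that alpha: about 80% at ICC 0.05 under the plan's own design factor. The power at the pilot ICC can be shown beside it. This takes a few sentences and no new data, and should be done before the analysing statistician is unblinded.

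A closed procedure is an acceptable alternative: a global 2-df test of arm at 5%, then each pairwise contrast at 5% only if the global test is significant. With exactly three arms it controls the familywise error strongly. In the simulation mentioned above, nurse against usual care had about 63% power with Bonferroni and 69 to 79% with the closed test, depending on the GP arm, so part of the loss is recovered. Those levels should be compared only with each other, since they carry the design-factor discrepancy. The closed test cannot exceed the unadjusted pairwise power (89.6% at 305), so it does not by itself restore 90%, and its power would also have to be restated. Its price is that no pairwise claim can be made without a significant global test.
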